### **2.2.4 Task load of medical team**

The NASA (National Aeronautics and Space Administration) Task Load Index (NASA-TLX) will be used to measure the task load of the first surgeon, first assistant, and instrument nurse immediately after the surgery in both groups.

### **2.2.5 Telesurgery monitoring data**

To characterize the status of the telesurgery system, the following data will be collected:

1. Round-trip network latency (for telesurgery): The round-trip network latency is defined as the time latency of data packages between transmission and reception.

2. Display latency (for telesurgery): The display latency is defined as the time latency between coding and encoding the endoscope image.
3. Frame loss (for telesurgery): The frame loss is defined as the loss of data packages during data transmission.
4. Malfunction: The malfunction of the local surgical robot or telesurgery system will be recorded. The local surgical robot or telesurgery system is tested systemically one day preoperatively. A malfunction of the telesurgery system is defined as the system being out of control for any reason, such as a telecommunications pathway fault, a laboratory pathway fault, or a robotic fault. A malfunction of the local surgical robot is defined as the robot being out of control for any reason.

### **3 STUDY DESIGN**

#### **3.1 Overall Design**

This prospective, multicenter, single-blinded, non-inferiority, randomized controlled trial will explore and compare the safety and reliability of telesurgery and local surgery for urologic procedures. The primary and secondary outcomes will be measured or recorded in the 6 weeks postoperatively.

Patients who have prostate cancer and a renal tumor, including renal cancer and a benign renal tumor, and who will undergone partial nephrectomy will be screened and asked to participate in this trial. The

participants will be randomized 1:1 to the telesurgery group or local surgery group. The follow-up time for the participants will be 6 weeks. The participants will be recruited from Chinese PLA General Hospital, Harbin Medical University Affiliated Cancer Hospital, the First Affiliated Hospital of Zhejiang University School of Medicine, the First Affiliated Hospital of Anhui Medical University, and the First Affiliated Hospital of Xinjiang Medical University. All participants will sign the informed consent form (ICF) and be screened for eligibility. Their basic information will be collected for clinical research.

### **3.2 Randomization**

This study will adopt a random number distribution system. The random grouping table of subjects will be generated by independent statisticians (who will not participate in the clinical trial) from random coding units. The ratio of the test group to the control group will be 1:1. The seed number for generating the random table is fixed, and the process of generating the random table can be repeated. The generated random table of subjects will be imported into the random system by the random system administrator. All random numbers will not be used twice. After the successful screening of subjects, the random responsible person of each center will log in to the system and enter the basic information of subjects according to the system prompts, including the date of birth and

the name abbreviation, etc. The system will generate a unique random number for each subject and randomly allocate subjects to the groups.

### **3.3 Blinding and Unblinding**

The patients will be blinded. Due to the significant differences in appearance between the experimental and control devices, blinding the researchers will not be possible. Blinding of the patients will be broken until this trial is finished.

### **3.4 Study Treatment**

#### **3.4.1 Surgeon and unit accreditation**

The surgeon's experience and habits can impact various aspects of surgical performance, such as safety, operative time, and outcomes. For this trial, surgeons should complete more than 500 robot-assisted laparoscopic surgery procedures, including prostatectomy and partial nephrectomy. The surgical approach will be determined according to the protocol of the trial hospital where the patient is situated to facilitate the generalizability of the findings.

#### **3.4.2 Structure of the telesurgery system and protective measures**

The telesurgery system mainly consists of three subsystems: a surgical robotic subsystem, a telecommunications subsystem, and a teleconference subsystem. The robotic subsystem will consist of a main surgeon console

in the first surgeon's hospital or laboratory and a patient cart in the operation room of the patients' hospital. For safety purposes, a backup surgeon console will be positioned on the patient side in the operating room. In the event of a malfunction with the telesurgery system, the surgeon will take control of the surgery and complete the subsequent types. The telecommunication subsystem will consist of the router and communication line, which will be provided by the network operator. The teleconference subsystem, which can transmit the audio and visual input of the first surgeon and operating room, will be used for communication between the first surgeon and the assistant. The video documentation of all telesurgery procedures will be recorded by the teleconference subsystem. The video documentation of local surgery will also be recorded.

The status of the telesurgery system for the telesurgery group will be monitored by the technique group.

As a protective measure to ensure the safety of the telesurgery, the robotic subsystem has been updated. When the network latency is  $> 200$  ms, the patient cart will stop working, and the telesurgery technique team will inspect and repair the mechanical malfunction of the system. Due to the prolonged duration required to rectify the issues, the surgeon

positioned at the patient's side will take control of the surgery using the backup console and proceed with the remaining surgical steps.

### **3.4.3 Proctoring of surgery and dissemination of a standard technique**

In this trial, robot-assisted laparoscopic prostatectomy and partial nephrectomy will be performed by the surgeon team. To reduce surgical heterogeneity, all procedures should adhere to standardized protocols, and all surgeons should receive in-person instruction and accreditation from [name] before the start of this trial. In prostatectomies, pelvic lymph node dissection will be carried out when the Gleason score of the prostatic biopsy is  $\geq 4+3$ . The anterior approach, which is the most common approach for prostatectomy, will be used. A transperitoneal or extraperitoneal approach can be selected by the medical team of each hospital and the first surgeon. For partial nephrectomies, the retroperitoneal approach should be the main approach.

### **3.4.4 Operation process of the telesurgery system**

In the telesurgery group, the first surgeon will activate the main console and the teleconference subsystem on the surgeon's side, and the patient's side will activate the teleconference system, surgical cart, and backup console of the surgery robot. Telesurgery technical teams in Beijing and Urumqi/Harbin/Hangzhou/Hefei/Haikou will be responsible for the

network connection and equipment debugging between the doctor's console and the patient's surgical platform. After the correct connection and conditions of all the subsystems of the telesurgery, all the display screens will be turned off, and the patient will be taken to the operating room for the surgery. After the patient is anesthetized, all display screens will be turned on again, which is due to blind considerations.

### **3.5 Standard Follow-up for Patients and the Medical Team**

Patients and medical team members will be followed up by the follow-up team of each center for this trial. Patients will be followed up three times, including at baseline (before the surgery), and 4 and 6 weeks after the surgery. The task load of the surgeon, first assistant, and instrument nurse will be measured immediately after the surgery. For telesurgery, the task load will be measured by the follow-up groups of the surgeon and patient sides together. Patients will continue to receive routine clinical follow-ups, and secondary outcomes will be measured up to 48 weeks.

### **3.6 Trial Assessments**

Trial assessments will be conducted at certain time intervals (defined around the date of surgery):

- (1) Baseline:** Data will be recorded before the surgery.
- (2) Perioperative:** Operative details, task load of the medical team, and status monitoring data of the telesurgery system, including the operation

details, obvious side injury, and surgery video, and monitoring data of the telesurgery system, will be collected immediately after the surgery.

**(3) In-hospital postoperative:** The time to hospital discharge, length of days in critical care, reoperation intervention in the hospital, and blood transfusion rates will be recorded according to the clinical information system of each site.

**(4) Four and six weeks after the surgery:** The complications, tests, and questionnaires will be recorded or measured at 4 and 6 postoperatively. Further follow-up will continue to be performed at longer time points, including 12 weeks, 24 weeks, and 48 weeks.

**The time point of the primary outcome is the finishing time of the surgery.** The completion of surgery is defined as all the planned steps of the operation being finished without any conversion or obvious side injury. After the surgery, the blood loss, surgical approach, and any other surgical details will be recorded by the medical team.

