**The secondary outcome measures include the following:**

**QoR-15 Score:** The QoR-15 score will be measured at baseline (before the surgery) and 4 and 6 weeks after surgery. The QoR-15 score is a patient-reported outcome questionnaire that measures the quality of postoperative recovery and fulfills the requirements for outcome measurement instruments in clinical trials.

**EPIC-26 Score:** The EPIC-26 score will be measured at baseline (before the surgery) and at 4 and 6 weeks after surgery.

**30-second chair-to-stand test:** The 30-second chair-to-stand test will be measured at baseline (before the surgery) and at 4 and 6 weeks after surgery.

**Clavien-Dindo complication system:** The Clavien-Dindo classification of surgical complications is a simple and widely used tool to assess and report postoperative complications in urologic surgery. The scores will be recorded at 4 and 6 weeks after the surgery.

**Operative:** Intraoperative surgical details will be recorded to compare telesurgery and local surgery. The conversion rate, operative blood transfusion rate, intraoperative blood loss, operative time, and warm ischemia time (for partial nephrectomy) will be recorded.

**Postoperative:** The postoperative conditions of the patients can reflect the effects and success of the surgery. Postoperative hospitalization days, length of days in critical care, reoperation intervention, the postoperative blood transfusion rate, and the mortality rate will be recorded through the clinical information system.

**Oncological outcomes:** The oncological outcomes for prostate cancer and renal cancer patients are key factors in the prognosis. After the surgery, the cancer sample will be viewed by two blinded pathologists.

The surgical margin rate will be focused.

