| Whether the operation
was successful or not           |           | ●                          |                 |                 |
| Operation time                                           |           | ●                          |                 |                 |
| Blood loss volume                                        |           | ●                          |                 |                 |
| Blood transfusion
volume                              |           | ●                          | ●               |                 |
| Surgery conversion                                       |           | ●                          |                 |                 |
| Task load of the
medical team                         |           | ●                          |                 |                 |
| Telesurgery system
monitoring indicators  |           | ●                          |                 |                 |
| Length of days in
hospital                            |           |                            | ●               |                 |
| ICU time                                                 |           |                            | ●               |                 |
| Positive margin of
tumor sample           |           |                            | ●               |                 |
| 30 second chair to
stand test             | ●         |                            | ●               | ●               |
| QoR-15 scale                                             | ●         |                            | ●               | ●               |
| EPIC-26 Scale                                            | ●         |                            | ●               | ●               |

|                                                    |  |   |   |   |
|----------------------------------------------------|--|---|---|---|
| Complication                                       |  | ● | ● | ● |
| Re-hospitalizations
and emergency
operations |  | ● | ● | ● |
| Mobility                                           |  | ● | ● | ● |
| Instrument
malfunction                          |  | ● |   |   |
| Record adverse events                              |  | ● | ● | ● |

1. These preoperative examinations will be performed by the medical system at the trial sites.

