2. Preoperative pathological reports for patients with prostate cancer will be collected by the medical system at the trial sites or via paper reports from other hospitals.

3. The status of the surgical margin will be collected by the pathological report of the tumor, which is reviewed by one or two blinded pathologists.

4. The 30-s chair-to-stand test at baseline will be tested by the nurse before the surgery. In the follow-up period, this test will be performed in the outpatient service by the doctor. If the patients cannot go to the surgery hospital, this test will be performed by the follow-up nurse via WeChat (A widely popular social app in China that can perform various operations such as questionnaire investigation, voice and video).

5. The monitoring status of the telesurgery system will be collected by the telesurgery technique team.

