#### **4.2.2 Perioperative morbidity**

To assess perioperative morbidity, the following clinical data will be collected:

1. Surgery-associated factors: intraoperative blood loss, operative time, and warm ischemia time (for partial nephrectomy).
2. Complications and adverse events: Adverse events will be recorded

using the Clavien-Dindo classification at 4 weeks and 6 weeks postoperatively.

3. Postoperative hospitalization days.
4. Length of days in critical care.
5. Reoperational intervention.
6. Readmission to the hospital: Readmission to the hospital for any reason will be recorded, and the surgery-associated condition will be systemically reviewed.
7. Intra- and postoperative blood transfusion rates.
8. Mortality rate.

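### Reoperation is limited to the hospital stay in protocol 3.6(3) but followed to 6 weeks in the assessment table, and the SAP fixes no counting window for reoperation, transfusion or death

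*Combined protocol and SAP*

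**What the plan says.** Protocol 2.2.2 and SAP 4.2.2 list reoperation, transfusion and mortality as secondary outcomes of perioperative morbidity. Neither gives a counting period for them. Transfusion is listed as "Intra- and postoperative blood transfusion rates".

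Protocol 3.6 deals with these outcomes twice. Item (3), headed as the in-hospital postoperative period, states that "reoperation intervention in the hospital, and blood transfusion rates will be recorded according to the clinical information system of each site". Item (4), for the later visits, names other things: "The complications, tests, and questionnaires will be recorded or measured at 4 and 6 postoperatively". The paragraph on postoperative measures, still within 3.6, then says that "reoperation intervention, the postoperative blood transfusion rate, and the mortality rate will be recorded through the clinical information system", with no in-hospital limit and no end date.

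The assessment table in protocol 5 has a row "Re-hospitalizations and emergency operations" marked at Visits 2, 3 and 4, where Visit 4 is 6 weeks ±3 days. It has a row "Blood transfusion volume" marked at Visits 2 and 3 only. No row is labelled mortality; one is labelled Mobility.

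Two general statements also apply. Protocol 3.1 places the primary and secondary outcomes within 6 weeks of surgery. Protocol 3.5 says that secondary outcomes are measured up to 48 weeks, and 3.6(4) adds contacts at 12, 24 and 48 weeks.

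**The concern.** A rate needs a defined event, a start, an end and a source. For reoperation the documents offer at least three ends (discharge, 6 weeks, 48 weeks) and two event labels (reoperation and emergency operation). The SAP is where an analyst would look for the answer, and it repeats the outcome list without a window. SAP 8.3.2 names the tests but not the counting rule. Because the researchers are not blinded (protocol 3.3), a rule left open now could be chosen after the results are known.

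The source adds a second gap. A site's clinical information system may hold later events treated at that site, but nothing says how an event treated elsewhere would reach it. No section provides for asking the patient about operations or transfusions at other hospitals.

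The trial's stated purpose is safety, and these are among its hardest safety outcomes. If 3.6(3) is followed, a post-discharge reoperation could show up under readmission or Clavien-Dindo grade and yet be missing from its own row.

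**Working it through.** **The plan's own figure.** Inputs from protocol 9.2: one-sided α 0.025, power 80%, success 98% in both arms, margin 10 points.

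n per arm = (1.960 + 0.842)² × (0.98 × 0.02 + 0.98 × 0.02) / 0.10² = 7.849 × 0.0392 / 0.01 = 30.77, rounded up to 31. This agrees with the plan, which enrols 34 per arm to allow for dropout. None of the three outcomes discussed here enters this calculation.

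**The sections side by side.**

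| Place | Reoperation | Transfusion | Death |
|---|---|---|---|
| Protocol 2.2.2, SAP 4.2.2 | Listed, no window | Rate, no window | Rate, no window |
| Protocol 3.1 | 6 weeks (all outcomes) | 6 weeks | 6 weeks |
| Protocol 3.5 | Up to 48 weeks (secondary outcomes) | Up to 48 weeks | Up to 48 weeks |
| Protocol 3.6(3) | In hospital, site system | Under the in-hospital heading, site system | Not named |
| Protocol 3.6(4), weeks 4 and 6 | Not named | Not named | Not named |
| Protocol 3.6, postoperative paragraph | Clinical information system, no limit | Same | Same |
| Protocol 5, table | Emergency operations, Visits 2 to 4 | Volume, Visits 2 and 3 | No row of that name |
| Protocol 13.1 and 13.2 | – | – | A serious adverse event, entered in the CRF |

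**Two test cases for reoperation.**
1. A patient is discharged and has a reoperation between Visit 3 and Visit 4. It is outside 3.6(3), inside the table row (if it was an emergency), and inside 3.1 and 3.5.
2. A patient has a reoperation after Visit 4 but before 48 weeks. It is outside 3.6(3), the table and 3.1, and inside 3.5.

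No section says which takes precedence, so the count depends on the section followed.

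**Size.** One event in 34 is 1/34 = 2.9 percentage points (1/31 = 3.2 if only the 31 required patients are analysed). Two events against one would be 2/34 = 5.9% against 1/34 = 2.9%.

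**How likely a difference is (illustration only).** The documents give neither event rates nor the share of events after discharge, so both are assumed. With event probability r and post-discharge share s, the chance that an in-hospital count misses at least one event among 68 patients is 1 − (1 − r × s)^68:
- r = 2%, s = 25%: 1 − 0.995^68 = 29%
- r = 5%, s = 50%: 1 − 0.975^68 = 82%
- r = 10%, s = 75%: 1 − 0.925^68 = over 99%

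The range is too wide to predict the number missed.

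**The case against.** The strongest reply is that protocol 3.1 already supplies a default of 6 weeks, and that 3.6(3) merely groups items by when and where they are collected. The postoperative paragraph of 3.6 supports this by repeating the outcomes without the in-hospital limit. This stands in part: 3.6 is not uniformly in-hospital. But 3.6(3) attaches the limit to reoperation in words, and 3.5 sets a different general window, so the default does not decide the matter.

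Four stronger readings are tempting, and the documents do not support them.

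- *That the transfusion windows contradict each other.* The Visit 3 mark may be only a collection date: "Length of days in hospital" and ICU time are marked in that column alone, and both are in-hospital quantities. What remains is a missing window and a volume recorded where a rate is to be reported.
- *That deaths away from the site would be lost.* Adverse events leading to death are serious adverse events and go into the CRF (protocol 13.1 and 13.2), and adverse events are recorded at the 4- and 6-week visits. What is missing is a rule that these deaths enter the mortality rate.
- *That under-counting would favour the non-inferiority conclusion.* That test covers surgical success alone, which is fixed at the end of surgery. The secondary outcomes have no margin. Proportional under-counting in both arms would shrink an absolute difference but leave a ratio unchanged.
- *That the plan expects care elsewhere.* Footnote 4 to the table says "If the patients cannot go to the surgery hospital, this test will be performed by the follow-up nurse via WeChat", but it concerns only the chair-to-stand test. It also shows that patients who cannot return are still contacted.

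It is also fair to say that matching the table's emergency operations to reoperation is an inference. It is a reasonable one, since no other row names a later operation, but the differing labels need to be reconciled.

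**Conclusion.** The point holds for reoperation: the same post-discharge event is counted or not according to the section followed, and the SAP does not resolve it. For transfusion and death it holds in a weaker form. Both are drawn from the clinical information system without a window of their own, the form in which transfusion is recorded does not match its outcome, and deaths reported as serious adverse events are not tied to the mortality rate.

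The firm figure for size is 2.9 percentage points per event in an arm of 34. How many events are at stake cannot be derived from the documents. Any percentage loss would simply restate an assumed post-discharge share. The primary outcome, the non-inferiority test and the sample size do not change. This is worth correcting because it decides which events enter the safety rates, and correcting it is cheap.

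**What to change.** Amend protocol 2.2.2, 3.6 and 5 and SAP 4.2.2 so that they agree:

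- Use one counting window for reoperation, transfusion and death: from surgery to Visit 4 (6 weeks ±3 days), in line with protocol 3.1, and at any hospital.
- Delete the in-hospital qualifier on reoperation in 3.6(3), and use one term for reoperation in the text and the table.
- Ascertain all three from the site system plus a direct question at the existing 4- and 6-week contacts.
- Count deaths recorded as serious adverse events in the mortality rate.
- Mark transfusion at Visit 4 as well, and record it as yes/no alongside the volume.
- Reconcile 3.1 with 3.5 by stating that any data collected to 48 weeks are reported separately.

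The cost is wording changes and three extra questions at contacts that already take place. Reported rates may be slightly higher than under an in-hospital count.
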